## Methods

### Overview

We will conduct a mixed methods study that integrates formative research and evaluative components into iterative improvement cycles. The planned interventions will examine the feasibility and document the process and challenges of implementing an audit system at scale. The study was also registered on ClinicalTrials.gov (NCT05640050).

### Study Setting

The study will be conducted in 1 district—Matiari (Sindh) with a population of 770,040 (Pakistan Bureau of Statistics–2017). The district selection was based on the operational ease with past positive experiences in efficient rollout of health services. Moreover, the district health office (DHO) of Matiari is actively involved in DHIS feedback meetings to improve the data quality.

### Study Population

The eligible population includes all women who had deliveries at community and health facilities that result in a maternal death or maternal “near miss,” stillbirths, or neonatal death (perinatal death).

### Inclusion Criteria

Women aged between 15 and 49 years who reside in the selected district are eligible to participate. Secondary-level public health facilities that offer obstetric and postnatal care and respective catchment areas supported by lady health workers (LHWs) are included in the study. Data for all maternal mortality, maternal “near misses,” and perinatal and neonatal mortality recorded for all women and newborns delivered at home (through LHW monthly reports) and who contact the health facility within 42 days after delivery, regardless of whether they delivered at the health facility, will be collected.

### Exclusion Criteria

Women who are nonresidents of the study district and who do not provide consent are not eligible to participate.

### Operational Definitions

The outcomes are defined in Textbox 1, using the International Classification of Disease–10 classification system by WHO [20].

Operational definitions—International Classification of Diseases–10.
**Stillbirth**
Stillbirth is the delivery of baby with no signs of life after ≥22 weeks of gestation.
**Neonatal mortality**
Neonatal mortality is the death of a newborn within the first 28 days of life.
**Perinatal mortality or death**
Perinatal mortality or death is a death that occurs around the time of birth. It can involve a still birth or be an early neonatal death that occurs up to 7 days after birth.
**Maternal *near miss***
Maternal *near miss* is a situation in which a pregnant woman nearly dies but survives a complication that occurred during pregnancy, during childbirth, or within 42 days of the termination of pregnancy. It can involve severe pregnancy-related complications (severe postpartum hemorrhage, severe pre-eclampsia, eclampsia, sepsis, and ruptured uterus) or critical interventions (blood transfusion, laparotomy, admission to an intensive care unit, hysterectomy, and other emergency surgical interventions in the abdominal cavity).
**Maternal mortality or death**
Maternal mortality or death is the death of a woman during pregnancy or within 42 days of delivery or the termination of pregnancy, irrespective of the duration or site of the pregnancy, from any cause related to or aggravated by the pregnancy or its management, but not from accidental or incidental causes.

### Sample Size

Population size is a challenge in the rural setting, however this study intend to cover all records of stillbirths, neonatal deaths, maternal deaths, and maternal “near misses” from four sources: (1) secondary health facilities, (2) LHW registers, (3) audit committee’s community representatives, and (4) project routine survey team.

### Study Timeline

The implementation of the audit system intervention is planned for 20-month period. To account for the effects of maturation (ie, 28 days after delivery for neonatal outcomes and 42 days after pregnancy for maternal near-miss outcomes), an additional 4 months will be added to the end of the intervention. Figure 1 Illustrates the implementation framework.

**Figure 1 figure1:**
[figure not shown]
Implementation framework.

### Audit System Implementation Phases (6 Phases)

The project development is based on formative studies that identified the importance of health care providers’ readiness, stakeholder and community participation, and health facilities’ readiness. The process will include consultative meetings with project’s core committee members, program advisory committee members, Director General of Health, and DHO staff.

#### Phase 1: Identify Facility and Community Leadership

The project’s core team and district manager identify facilities and community representatives who will coordinate and liaise with other district stakeholders to implement the community audit interventions.

#### Phase 2: Establish the Audit Committee

The person in charge of the health facility will establish an audit committee using existing health committees at the Tehsil Head Quarters, quality control committees, medical inspection committees, health welfare committees, and joint health inspection committees in health facilities at Matiari. Audit committees will be led by the medical superintendent of the hospital, with a member from administration, 3 to 4 consultants or medical officers from various departments (gynecologist; pediatrician; ear, nose, and throat [ENT] specialist; pathologist; head of the emergency department; and head nurse), district magistrate, or focal person from DHOs. The community engagement and audit system for project audit committee will be established at each facility; preferably, members will be at least 2 obstetricians, 2 pediatricians, 1 administrator, project focal person, and community representatives as community audit representative. Responsibilities and audit committee structure will be described. Members of the audit committee will update their credentials every month, and trickle-down training will be conducted by audit committee members.

#### Phase 3: Initiate Audit With Ongoing Community Engagement

Community representatives (1-3 individuals) will be identified as community audit representatives. They will be invited to attend the monthly audit meetings with facility-based audit committee members to discuss the community perspectives (delays 1 and 2) and other issues pertaining to the negative maternal and perinatal outcomes. LHWs, lady health visitors, community midwives (CMWs), male community mobilizer (village or otaq leader or any other active member of village), or any other influential women in the village will be engaged for audit committee decisions. They will provide timely oversight, monitor, and respond to adverse events and later confer in the audit meetings.

#### Phase 4: Train the Audit Committees

Training for audit representatives and members of the audit committee, will be conducted using 3-day training workshop, which includes the following:

Day 1: Maternal death, near misses, and perinatal death (stillbirth and neonatal deaths),Day 2: The Three Delays framework and identifying modifiable factors, andDay 3: Mentoring regarding the identification of the audit committees and initiating the audit implementation committee.

The audit committee will be trained to follow ethical guidelines in maintaining an empathetic gesture while recalling the adverse patient events by the respondents. Training will also include standardized case studies and completion of audit meeting minutes and action item tools.

#### Phase 5: Launch the Audit Cycle (Monthly Meetings)

##### Overview

The WHO audit system [20] will be adapted to assess maternal, perinatal, and neonatal deaths with 6 steps. Audit process in health facilities and communities is illustrated in Figure 2. Following are the steps and their processes involved in audit cycle.

**Figure 2 figure2:**
[figure not shown]
World Health Organization audit cycle. DHO: district health officer; LHW: lady health worker; MIS: management information system.

##### Step 1: Identifying Cases for Review

The district supervisors will record all maternal deaths, maternal near misses, deliveries, births, stillbirths, and neonatal deaths that occur in the delivery ward, neonatal unit, and postnatal ward, ensuring the capture of the minimum set of perinatal indicators in a source register. Efforts to collect and record data on maternal deaths, near misses, and perinatal and neonatal deaths that occur in the community will be made through monthly reporting from LHWs or CMWs to their associated health facility or by women who contact the health facility after delivery. Specific strategies will be put in place to ensure that all deaths are captured and filtered to the mortality audit committee, so that cases can be selected for review and discussion at the mortality audit meetings.

##### Step 2: Collecting Information

The aim is to empower designated staff to collect a standardized set of information from the patient file or register as soon as possible after the death. For every death, decisions will be taken regarding what information is recorded, where the information is recorded, who records it, and who collates it on a periodic basis both for the death review process and for reporting to other levels within the health system. It should be noted that if the use for the data cannot be identified, the data will not be collected. Before collecting the information, the audit committee will have a clear understanding of the data analysis plan to help identify the data to collect. Data abstraction or collection forms will be either electronic or paper-based, depending on the infrastructure and capacity of the health facility. Clear directions about the exact data and qualitative information that should be collected will be included.

All data collected will be stored on password-protected laptops or tablets or locked cabinets in locked offices within the health facility. Before implementation, data collection forms will be piloted and revised as needed. The minimum data collected will include the following: information about the mother’s condition, baby’s condition on admission and at the onset of labor (for antepartum and intrapartum deaths), baby’s condition at birth (stillbirth or live birth), baby’s condition on discharge from the health facility (alive, transferred to another facility, or dead], and date and time of birth and death (so that the age at death can be calculated in hours rather than days).

As part of the intervention, each facility audit system is planned to be comprehensive to ensure that it captures data on each death and includes the relevant cause of death; link to maternal condition; demographic data; and a list of contributing, modifiable factors corresponding to codes for analysis and linked to recommendations. To ensure that phase-1 and phase-2 delays are captured, all efforts to link deaths that occur in the community to the facility audit system will be conducted by the trained LHWs, CMWs, and project team. The audit committee will hold follow-up monthly meetings with designated community engagement members to initiate the chain of notifications within the audit cycle as it relates to the implementation of recommendations and solutions.

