**Methods:**

The implementation of the audit system comprises six phases: (1) identify facility and community leadership through consultative meetings with government district health offices, (2) establish the audit committee under the supervision of district health officer, (3) initiate audit with ongoing community engagement, (4) train the audit committee members, (5) launch the World Health Organization audit cycle (monthly meetings), and (6) quarterly review and refresher training. Data from all deliveries, live births, maternal deaths, maternal near misses, stillbirths, and neonatal deaths will be identified and recorded from four sources: (1) secondary-level care rural health facilities, (2) lady health workers’ registers, (3) community representatives, and (4) project routine survey team. Concurrent quantitative and qualitative data will be drawn from case assessments, process analysis, and recommendations as components of iterative improvement cycles during the project. Outcomes will be the geographic distribution of mortality to measure the reach, proportion of facilities initiated to implement an audit system for measuring the adoption, proportion of audit committees with community representation, and proportion of audit committee members’ sharing feedback regularly to measure acceptability and feasibility. In addition, outcomes of effectiveness will be measured based on data recording and reporting trends, identified modifiable factors for mortality and morbidity as underpinned by the Three Delays framework. Qualitative data will be analyzed based on perceived facilitators, barriers, and lessons learned for policy implications. Results will be summarized in frequencies and percentages and triangulated by the project team. Data will be analyzed using Stata (version 16; StataCorp) and NVivo (Lumivero) software.

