### History of Perinatal Audit Systems in Pakistan

Previous efforts to introduce facility audit systems by the Pakistan Ministry of National Health Services, Regulations, and Coordination have used the phased implementation of the Maternal and Perinatal Death Surveillance and Response to enhance reporting, recording, tracking, and auditing of deaths [17]. The World Health Organization (WHO) is currently assisting Khyber Pakhtunkhwa and Baluchistan provinces, and United Nations International Children’s Emergency Fund (UNICEF) is helping the Sindh province in implementing audit mechanisms, but results have not been made public. The United Nations brief on COVID-19 [18] and the Pakistan Health Report 2020 [19] have stated that the Maternal and Perinatal Death Surveillance and Response has great potential for success.

We hypothesize that a WHO audit cycle that is locally acceptable in close consultation with local community representatives and health care providers is feasible for implementing a robust audit system in rural settings. Specifically, we asked the following questions:

Is the implementation of facility-based maternal and perinatal mortality audits in combination with targeted community engagement feasible in rural Pakistan?Will the maternal and perinatal audits improve the reporting of deaths and maternal near misses at the DHIS health facilities?Will the audit systems help better identify medical and nonmedical factors of deaths and near misses, and how doable recommendations are implemented through integration of feedback loops within the health facilities and communities?Will the community-facility audit interaction improve the early referral proportions?

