### Secondary Outcomes

The secondary outcomes include the following:

Geographic distribution of mortality to measure the percentage coverage or reach in the implementation district,Change in trends in data recording and reporting to measure effectiveness,Categorization of mortality and maternal near-miss cases among Three Delays framework,Number of awareness sessions covering the proportion of the catchment population,Number of referrals in and out of the health facility,Number of transport mechanisms linked to health facilities by audit committee members, andProportion of health facilities implementing actionable recommended actions at the facility level.

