##### Step 6: Monitoring and Evaluation

In addition to the monthly audits, the project committee will also collect administrative and survey data to capture the process and outcome indicators. From independent, third-party surveys and data sources such as DHIS, facility registers, and LHW management information system, the impact of the intervention will be evaluated based on the maternal perinatal and neonatal mortality and morbidity outcomes and rated for all pregnant women, mothers, and newborns.

The model will contain audit guidelines, protocols, and training materials and tools for effective monitoring at the facility level in the targeted districts with their respective catchment populations. A monthly monitoring cycle will be set up within the implementing facilities to ensure effective implementation of the audit systems.

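### The reporting-trend outcome is not limited to routine channels, so cases found by the project's own staff could raise it without any effect of the audits

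*Protocol article*

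**What the plan says.** Three parts of the protocol article bear on this.

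- **The question and the outcome.** The Introduction (History of Perinatal Audit Systems in Pakistan) asks: "Will the maternal and perinatal audits improve the reporting of deaths and maternal near misses at the DHIS health facilities". Secondary Outcomes lists "Change in trends in data recording and reporting to measure effectiveness", and the Methods paragraph of the Abstract says that "outcomes of effectiveness will be measured based on data recording and reporting trends".
- **Who finds the cases.** Sample Size and the Abstract name four sources of deaths and near misses: secondary facilities, LHW registers, community representatives and, as the last item, "4) project routine survey team". Phase 5, Step 1 describes the ordinary community route as "monthly reporting from LHWs or CMWs to their associated health facility", or contact by the woman herself after delivery. Step 2 adds project staff, with the wording "link deaths that occur in the community to the facility audit system will be conducted by the trained LHWs, CMWs, and project team".
- **The comparison.** Study Setting names a single district, and no control area is described anywhere. Data Management and Analysis describes descriptive statistics. No section says that cases found by project staff are left out of the reporting trend or tabulated apart from the others.

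**The concern.** The second research question is causal: do the audits improve reporting? The answer is to be read from a trend in recorded and reported cases. Over the same period the project runs its own case-finding and helps bring community deaths into the facility audit system. If those cases are counted, reported deaths go up because extra people are searching. Facility staff and lady health workers need not report any better.

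With no comparison area and a descriptive analysis, nothing else in the design as described separates the two explanations. The Conclusions promise evidence on scale-up. A gain produced by project staff may disappear when they leave, so a district relying on the result could expect an improvement that routine services do not deliver.

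**Working it through.** The article gives no target, baseline or power for the reporting outcome, so there is no stated figure to reproduce. The check is a reading of the text followed by an illustration.

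**Reading.**
1. Effectiveness is the change in recording and reporting (Abstract, Secondary Outcomes).
2. Project staff are a source from which cases are identified and recorded (Abstract, Sample Size), and they share the linking of community deaths to the facility audit system (Step 2).
3. The article does not say whether the trend is counted in the audit database, the source register or DHIS.
4. Project-found cases can therefore add to the counted trend unless the count is restricted, and no restriction is stated.

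Step 3 is the weak link. The bias exists only if project-found cases are in the system where the trend is counted.

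**Illustration.** Let F be the share of deaths that occur in facilities and C the share at home or in route. Let f be the share of facility deaths recorded at baseline, r the share of community deaths recorded at baseline, and s the share of the missed community deaths that project staff add to the counted records. With true deaths constant and routine reporting unchanged:

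apparent rise = s × C × (1 − r) / (f × F + r × C)

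From the neonatal row of Table 1, F = 55.3 + 2.3 = 57.6% and C = 38.2 + 4.1 = 42.3%. The values of f, r and s are assumptions; the document gives none of them.

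| f | r | s | Calculation | Apparent rise |
|---|---|---|---|---|
| any | any | 0 | project-found cases not counted | 0% |
| 1 | 0 | 0.25 | 0.25 × 42.3 / 57.6 | 18% |
| 1 | 0 | 0.50 | 0.50 × 42.3 / 57.6 | 37% |
| 1 | 0 | 1.00 | 42.3 / 57.6 | 73% |
| 1 | 0.5 | 0.50 | 0.50 × 21.15 / (57.6 + 21.15) | 13% |

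A baseline f below 1 makes the rise larger; some community reporting at baseline makes it smaller, as the last row shows.

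A lower assumed baseline gives larger figures. If 40 of 100 true deaths are routinely reported and project staff add 30% to 70% of the other 60, the count becomes 40 + 0.3 × 60 = 58 to 40 + 0.7 × 60 = 82, a rise of 45% to 105%. These figures show only that the mechanism can matter. They do not estimate the bias in this study.

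**The case against.** Several points can fairly be made for the plan.

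- **Audit system and DHIS are not the same thing.** Step 2 brings community deaths into the audit system so that the first two delays are captured, whereas the research question is about reporting at DHIS facilities. A reader might infer that project-found deaths are entered into DHIS. No section says so. This stands, and it is why the point is conditional.
- **An independent measure may exist.** Step 6 evaluates impact "From independent, third-party surveys and data sources such as DHIS, facility registers, and LHW management information system". A reader might infer that these surveys are the project's own survey team under another name, so that the article contradicts itself or has used up its only yardstick. The text never equates the two, and they may be separate. However, Step 6 names these sources for mortality and morbidity impact, not for completeness of reporting, so they do not settle the matter as written.
- **The project focal person.** A reader might count this committee member as a further project channel for cases. Phase 2 gives the role membership only, with no case-finding task.
- **Capture is part of the intervention.** Step 2 presents comprehensive capture as an intended component, and Limitations adds refresher training on registers and DHIS. A rise could properly be credited to the whole package. That does not answer a question about the audits, nor show what would remain without project staff.
- **Detail left to fuller documents.** An article need not print every numerator, and silence is not evidence that sources will be pooled. But the article does fix who finds cases and what measures effectiveness. The source of first notification also has to be noted when the case is recorded; an analysis plan cannot recover it later.

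**Conclusion.** The concern holds in a conditional form. As written, the reporting trend can be raised by project case-finding, and the described design offers no way to tell that apart from an effect of the audits. The conclusion rests on one assumption that the document neither confirms nor excludes: that at least some project-found cases enter the records in which the trend is counted. The size is unknown; every percentage in the illustration depends on assumed detection and baseline reporting. The outcome affected is secondary. The primary outcomes (adoption, feasibility, acceptability) are not touched. It is worth correcting because it bears on a stated research question and on the scale-up message, and because the remedy must be in place when cases are recorded.

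**What to change.** 1. Add a field to the case form for the source of first notification: facility staff, LHW or CMW, community representative, or project team.
2. For the second research question and the reporting-trend outcome, count only cases first notified through routine channels (DHIS, facility registers, LHW management information system), and state in which system the trend is counted.
3. Report completeness as the share of deaths and near misses identified by the project survey that routine returns had also reported independently.

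Cases need not be held back from the audit committee. A waiting period until monthly returns close would delay the intervention and conflict with Step 2, which wants information gathered promptly after a death. The source field does the work without it.

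The cost is one extra field and the discipline to complete it. The reported improvement may look smaller, partly because a death that project staff reach first is not counted even if routine staff would have reported it later.
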